#### Imaging data acquisition

MRI scans will be performed at the Huaxi MR Research Center, West China Hospital. An experienced radiologist will acquire brain images using a 3.0 T Prisma scanner (Siemens Healthcare, Erlangen, Germany) with a 64-channel head coil. All participants will undergo a T2-weighted fluid-attenuated inversion recovery (FLAIR) scan to exclude cerebral organic lesions (such as stroke and tumor) prior to formal experimental scans. After the exclusion of cerebral organic lesions in each participant, high-resolution T1-weighted imaging (T1WI), ^1^H-MRS, and rs-fMRI data will be acquired sequentially. During imaging data acquisition, participants will be instructed to relax and stay awake with closed eyes, and foaming pads will be used to reduce head motion.

T1-weighted images will be acquired using a 3D Magnetization Prepared Rapid Gradient Echo (3D-MPRAGE) sequence with the following parameters: repetition time (TR): 1500 ms, echo time (TE): 1.87 ms, field of view (FOV): 256 mm × 256 mm, and slice thickness: 0.8 mm. Single-voxel ^1^H-MRS data will be obtained using a point-resolved spectroscopy (PRESS) sequence with the following parameters: TR: 2000 ms, TE: 30 ms, FOV:240 mm × 240 mm, volume of interest (VOI): 40 mm × 15 mm × 20 mm, and flip angle: 90°. The bilateral hippocampi will be selected as the regions of interest (ROIs), and saturation bands will be applied around the ROIs to suppress confounding signals from the surrounding cerebrospinal fluid (CSF), skull, and blood vessels. Procedures such as shimming and water suppression prior to formal data acquisition will be automatically performed by the MRI scanner. Spectral data, both with and without water suppression, will be obtained. We will use the internal water signal as a reference for eddy current correction and absolute metabolite quantification. The scan parameters for the rs-fMRI images will be as follows: gradient-recalled echo echo-planar imaging (GRE-EPI) sequence, TR: 2000 ms, TE: 37 ms, slice thickness: 2 mm, and FOV: 208 mm × 208 mm.

#### Imaging data preprocessing

##### ^1^H-MRS data

Raw MRS data will be analyzed using the linear combination model (LCModel, version 6.3-1H, http://s-provencher.com/lcmodel.shtml). A total of two investigators will examine the data independently. Only spectra that meet the following criteria will be included in the subsequent analysis: Signal-to-noise ratio (SNR) ≥ 10, full width at half maximum (FWHM) ≤ 0.08 ppm, and Cramer–Rao lower bound (CRLB) < 15%. The metabolites to be measured will include choline (Cho), total creatine (Cr), glutamate (Glu), glutamine (Gln), lactate (Lac), myo-inositol (Ins), N-acetylaspartate (NAA), glycerophosphorylcholine (GPC), and glutathione (GSH). The final metabolite concentration will be expressed in mmol/kg wet weight.

To eliminate the partial volume effect of cerebrospinal fluid (CSF), we will use the cortical thickness procedure named Advanced Normalization Tools (ANTs) to segment T1-weighted images of each participant to obtain the whole-brain proportions of the gray matter, white matter, and CSF. The proportions within the voxel will then be determined by overlaying the voxel coordinates onto the segmented T1-weighted images. Finally, CSF-corrected metabolite concentrations will be calculated according to the following formula: C*
_cor_
* = C*
_raw_
* × [V*
_total_
* / (V*
_total_
*-V*
_CSF_
*)], where *C_cor_* is the corrected results, *C_raw_* is the uncorrected results of the whole voxel, *V_total_* represents the total volume of the voxel, and *V_CSF_* is the volume of CSF.

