##### Secondary outcome measures

Cognitive measures include the following: Baseline-to-endpoint (week 8) changes in the Digit Span Forward Test (DST-F), the Trail Making Test Part A(TMT-A), immediate and delayed recall of the Rey Auditory Verbal Learning Test (RAVLT), copy trial, immediate and delayed recall of the Rey–Osterrieth complex figure test (RCFT),the Trail Making Test Part B(TMT-B), the Digit Span Backward Test (DST-B), the Stroop Color and Word Test (SCWT), the phonemic fluency test, the category fluency test, the action fluency test, and the 30-item Boston Naming Test (BNT-30).Imaging measures include the following: Changes in NAA, Cho, Glu, Gln, Lac, Ins, GPC, GSH, and RSFC of each hippocampus at week 8.Clinical symptoms and quality of life measures include the following: Baseline-to-endpoint (week 8) changes in the Multidimensional Fatigue Inventory (MFI-20), Pittsburgh Sleep Quality Index (PSQI), Generalized Anxiety Disorder 7-item scale (GAD-7), 24-item Hamilton Depression Scale (HAMD-24), and 36-Item Short Form Survey (SF-36).

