#### Statistical analysis

Statistical analysis will be conducted by an appointed statistician blinded to group allocation using R software (version 4.2.1; R Foundation). Intergroup comparisons of RSFC will be performed using the DAPBI toolbox. Normally distributed continuous variables will be reported as mean±standard deviation, while non-normally distributed data will be reported as median [P25 P75]. A *p*-value of <0.05(two-tailed) will be set as the significance level for all analyses.

The intention-to-Treat (ITT) protocol will be used for the analysis of all outcomes. The ITT population will include all participants who are randomized, regardless of treatment adherence or protocol deviations. The missing value will be handled using multiple imputations.

First, intergroup comparisons of demographic data (such as age, sex, and educational level), illness duration, estimated premorbid intelligence function, and PA will be conducted to examine comparability across the three groups. Categorical data will be analyzed using the χ^2^ test. Normally distributed continuous variables will be tested using one-way analysis of variance (ANOVA), whereas the non-normally distributed data will be analyzed using the Kruskal–Wallis test.

Analysis of covariance (ANCOVA) will be applied to the primary outcome and other cognitive measures, with age, estimated premorbid intelligence ability, and PA as covariates. ANCOVA with age and PA as covariates will be used for clinical measures and brain metabolites. Repeated measures ANOVA will be used to compare differences in hippocampal functional connectivity among the three groups. Age, sex, and years of education will be included as covariates. *Post hoc* analysis will be performed for RSFC with interaction effects. Multiple comparisons for hippocampal functional connectivity will be corrected using cluster-level family-wise error (FWE) correction, with a significance threshold set at a p-value of < 0.05. The χ2 test will be used to compare the rate of AEs and SAEs between the groups. Finally, Spearman correlation analysis will be performed to examine the relationships between cognitive outcome measures and imaging indicators exhibiting intergroup differences.

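### The percent CRLB < 15% inclusion rule depends partly on the measured concentration, so for any metabolite near that limit it discards low values selectively and biases an arm difference toward zero

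*Protocol article*

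**What the plan says.** The protocol article, under Imaging data preprocessing (1H-MRS data), has the spectra fitted with LCModel and then sets an inclusion rule: "Only spectra that meet the following criteria will be included in the subsequent analysis", namely SNR ≥ 10, "full width at half maximum (FWHM) ≤ 0.08 ppm, and Cramer–Rao lower bound (CRLB) < 15" percent. The same limit covers all nine metabolites: Cho, Cr, Glu, Gln, Lac, Ins, NAA, GPC and GSH. No absolute limit, no cohort-level rule and no exception for a weakly measured metabolite is given.

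Eight of the nine are secondary outcomes, on each side: "Changes in NAA, Cho, Glu, Gln, Lac, Ins, GPC, GSH, and RSFC of each hippocampus at week 8". The Discussion makes Lac the marker of mitochondrial function and GSH the marker of oxidative stress.

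Under Statistical analysis, "ANCOVA with age and PA as covariates will be used for clinical measures and brain metabolites". The intention-to-treat "protocol will be used for the analysis of all outcomes", and "The missing value will be handled using multiple imputations". The text does not say whether values rejected for a high CRLB count as missing and are imputed, or are simply left out.

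**The concern.** A CRLB stated in percent has the estimate in its denominator. Two spectra with the same absolute fit uncertainty can therefore fall on opposite sides of 15% only because one participant has less of the metabolite. SNR and FWHM already screen spectral quality, so what the CRLB limit adds is partly a lower cut on the outcome variable itself.

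For a metabolite near the limit this has three consequences. Retained means are too high. If treatment moves the level, the share of week-8 values that survives differs between arms. A true arm difference in change is understated. Values lost in this way are missing because of their own size, so an imputation that assumes missing at random starts from the wrong premise.

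There is also a question of level. CRLB belongs to each fitted metabolite, but the rule is worded for spectra. Read literally, one weak metabolite would remove a well-fitted NAA or Glu value from the same spectrum. At stake is the metabolic half of the trial's mechanism question.

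**Working it through.** The article states no retention rate, concentration, absolute CRLB or metabolite effect, so it has no figure to reproduce. Its only input is the 15% limit; every other value below is an assumption.

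**1. What the rule does.** Percent CRLB = 100 × s / y, with s the absolute uncertainty and y the estimate. The condition < 15% is the same as y > s / 0.15 = 6.67 s, which is a lower cut on y.

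**2. One visit, cut on the value alone.** If a share p of normally distributed values is cut, put a = z(p) and λ = φ(a)/(1 - p). The retained mean rises by λ × SD, and the share of a small effect that survives is 1 - λ(λ - a). For p = 20%: a = -0.842, λ = 0.350, share = 1 - 0.350 × 1.192 = 0.58. For p = 5% it is 0.81, and for p = 50% it is 0.36.

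**3. Baseline and week 8, equal noise in every spectrum.** Assumed: true mean 1.10 mmol/kg, between-subject SD 0.20, extra week-8 SD 0.08, s = 0.14, VA effect -0.15.
- Cut: 0.14 / 0.15 = 0.933.
- Baseline SD of measured values: √(0.20² + 0.14²) = 0.244. Failing: Φ((0.933 - 1.10)/0.244) = Φ(-0.68) = 25%.
- Week-8 SD: √(0.20² + 0.14² + 0.08²) = 0.257. Failing: control Φ(-0.65) = 26%; VA, with mean 0.95, Φ(-0.06) = 47%.
- Retained baseline mean: 1.20 instead of 1.10.
- Difference in change among those retained at both visits (simulation, 1,000,000 per arm): -0.108 instead of -0.15. Loss = 1 - 0.108/0.15 = 28%.

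**4. Sensitivity of the loss in the same model.**

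| Uncertainty s | Noise between spectra | Effect -0.15 | Effect +0.15 |
|---|---|---|---|
| 0.05 | equal | negligible | negligible |
| 0.10 | equal | 7% | 3% |
| 0.12 | equal | 16% | 8–9% |
| 0.14 | equal | 28% | 18% |
| 0.16 | equal | 40% | not quoted |
| 0.14 | log-SD 0.2 | about 15% | not quoted |
| 0.14 | log-SD 0.3 | about 10% | 8% |
| 0.14 | log-SD 0.4 | about 6% | not quoted |

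With a true effect of zero the difference in change is 0.000 at every uncertainty tried, because both arms are cut alike.

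**5. Does imputation repair it?** A second model was used: mean 1, CV 20%, within-person correlation 0.5, uncertainty 12% of the mean with log-SD 0.15. Complete cases recover 0.82 of an effect of +15% and 0.72 of -15%. A normal-model fit under missing-at-random, which is the large-sample limit of such an imputation, recovers 0.75 and 0.62. In the same model with uncertainty 5% of the mean, complete cases recover about 0.99 at CV 20% and 0.93 to 0.97 at CV 30%.

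**The case against.** The strongest reply is that a CRLB limit is a quality rule and that noisy scans fail it as they should. SNR ≥ 10 and FWHM ≤ 0.08 ppm are one-sided limits, so accepted spectra still differ in noise, and the 28% figure depends on treating them as equal. This stands. Once noise varies, the loss falls to about 6% to 15%. A reader might infer that a value fails because its concentration is low; the accurate statement is that it fails on the ratio of noise to value, so low values fail more often.

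A reader might also infer that effects on Lac, GSH or Gln will be shrunk. The article does not support that. It names Lac and GSH as markers but gives no concentration or CRLB for any metabolite, so nearness to 15% is an assumption.

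Direction matters too. The Discussion reports GSH as reduced in ME/CFS and as rising with acupuncture in fibromyalgia. For an increase the loss in the example is 18%, not 28%.

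Nor does the rule create a false positive: with no true effect it produces no arm difference, so the inflated mean alone does not bias the randomised contrast. Only secondary imaging outcomes are affected.

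Finally, the imputation model may be set out in an analysis plan that is not shown. Its absence from an article is no fault. But the inclusion rule itself is fixed in the article, and imputation under missing-at-random would not undo it.

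**Conclusion.** The point holds in conditional form. The percent limit makes inclusion depend partly on the outcome. For a metabolite whose typical CRLB is near 15%, retained means are biased upward, retention can differ by arm, and a true difference in change is biased toward zero. That mechanism follows from the stated rule, and no scenario with an appreciable share of discarded values reversed the direction.

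The size cannot be fixed from the article. In the assumed example it runs from about 6% to 28% of an effect of -0.15, depending on how much noise varies between spectra, and is 18% for +0.15 at equal noise. It is nil or small for well-measured metabolites. The consequence is a lost or understated secondary finding, not a spurious one; the primary SDMT outcome and RSFC are not touched. The per-spectrum wording needs correction whatever the size.

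**What to change.** Before any unblinded look at the MRS data, rewrite the inclusion paragraph as follows.

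- Reject whole spectra only on SNR, FWHM and artefact review by assessors blinded to arm.
- Apply CRLB to each metabolite separately, so that a weak metabolite cannot remove a well-fitted one.
- Replace the individual percent cut-off by one of two preset rules: an absolute CRLB limit (mmol/kg), or a cohort-level rule that drops a metabolite for everyone if its median percent CRLB, pooled over arms at baseline, exceeds a stated limit. Under either rule, do not discard an individual value because it is low.
- Report the number of values retained by arm, visit and metabolite.
- Give the analysis with the 15% cut-off as a sensitivity analysis.
- State whether rejected values are imputed or excluded.

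The cost is one paragraph of text and no new data. The downside is that some noisier individual values are kept for weak metabolites, which costs precision. Weighting by absolute CRLB might recover part of that, but this has not been shown here.

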##### rs-fMRI data

The preprocessing of rs-fMRI data will be performed using the Statistical Parametric Mapping (SPM) 12 (Wellcome Trust Centre for Neuroimaging; http://www.fil.ion.ucl.ac.uk/spm) and the Data Processing and Analysis of Brain Imaging (DPABI) toolbox according to the following steps: (1) removal of the first 10 rs-fMRI images to allow for signal stabilization; (2) slice-timing correction; (3) realignment for head motion correction (excluding participants with head motion > 3 mm or head rotation > 3°);(4) normalization of functional images into Montreal Neurological Institute (MNI) space through the DARTEL alignment method and resampling to a voxel size of 3 × 3 × 3 mm^3^; (5) regression of nuisance covariates (including Friston-24 head motion parameters, global mean signals, white matter signals, and cerebrospinal fluid signals); (6) smoothing using a Gaussian kernel with a full width at half maximum (FWHM) of 6 mm; and (7) band-pass filtering (0.01–0.08 Hz) of the time series for each voxel to remove low-frequency drift and high-frequency noise.

The bilateral hippocampi will be selected as seed regions to perform seed-to-voxel RSFC analysis. These regions will be extracted from the Automated Anatomical Labeling (AAL) atlas. FC between each seed region and all other brain voxels (excluding the seed clusters) will be calculated using the DPABI toolbox. The mean time series of the left and right hippocampi will be extracted separately, and Pearson’s correlation coefficients will be calculated between the mean time series of each seed and the time series of all other voxels. The resulting correlation coefficients will then be *z*-normalized using Fisher’s *r*-to-*z* transformation. Finally, an RSFC map for each seed region will be generated for each participant.

#### Physical activity monitoring

Physical activity (PA) is a major factor that triggers the exacerbation of symptoms in patients with ME/CFS. To control the influence of variation in PA on study results, accelerometer-based PA monitoring will be performed. All participants will be instructed to wear an ActiGraph wGT3X-BT accelerometer (ActiGraph LLC, Pensacola, FL, USA) on the left wrist at all times throughout the 8-week trial period, except during sleep or water-based activities such as showering and swimming. Moreover, two appointed investigators will contact participants through WeChat (a social media platform in China) video calls between 8:30 a.m. and 9:00 a.m. each day to ensure adherence. The accelerometer-collected data will be exported every 2 weeks.

ActiLife version 6.13.4(ActiGraph Corporation) will be used to download and analyze the accelerometer data. The raw data will be converted into counts of movement using 60-s epoch lengths(ct/min). Non-wear time will be defined as zero accelerometer counts for any continuous 90 min. A day will be considered valid if the wear time is ≥ 10 h. Summary measures will be calculated using the average values across all valid days, including total PA time (min/day >100 ct/min), sedentary time (min/day for ≤100 ct/min), light PA time (min/day for 100–2019 ct/min), moderate PA time (min/day for 2020–5,998 ct/min), and vigorous PA time (min/day for ≥5,999 ct/min).

#### Outcomes

##### Primary outcome measure

The primary outcome is the change from baseline to week 8 in the SDMT score.

##### Secondary outcome measures

Cognitive measures include the following: Baseline-to-endpoint (week 8) changes in the Digit Span Forward Test (DST-F), the Trail Making Test Part A(TMT-A), immediate and delayed recall of the Rey Auditory Verbal Learning Test (RAVLT), copy trial, immediate and delayed recall of the Rey–Osterrieth complex figure test (RCFT),the Trail Making Test Part B(TMT-B), the Digit Span Backward Test (DST-B), the Stroop Color and Word Test (SCWT), the phonemic fluency test, the category fluency test, the action fluency test, and the 30-item Boston Naming Test (BNT-30).Imaging measures include the following: Changes in NAA, Cho, Glu, Gln, Lac, Ins, GPC, GSH, and RSFC of each hippocampus at week 8.Clinical symptoms and quality of life measures include the following: Baseline-to-endpoint (week 8) changes in the Multidimensional Fatigue Inventory (MFI-20), Pittsburgh Sleep Quality Index (PSQI), Generalized Anxiety Disorder 7-item scale (GAD-7), 24-item Hamilton Depression Scale (HAMD-24), and 36-Item Short Form Survey (SF-36).

##### Adverse events and safety

Any adverse events (AEs) or serious adverse events (SAEs) occurring during the intervention, whether related to the intervention or not, will be recorded in case report forms (CRFs) in detail (including the onset pattern, onset time, duration, severity, frequency, and treatment). Investigators will assess the relationship between AEs or SAEs and acupuncture treatment according to factors such as cause, timing, and clinical course. Common AEs related to acupuncture (including fainting, stuck needles, broken needles, bent needles, bleeding, edema, and other minor AEs) will be treated by the acupuncturist immediately. For SAEs, such as stroke recurrence or organ damage, researchers will immediately stop the treatment and send the patient to the emergency department. SAEs will be reported to the ethics committee within 24 h. The research team will bear the treatment costs for all AEs and SAEs.

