## Methods and analysis

### Study design

This is a prospective, three-armed randomized controlled trial using rs-fMRI and ^1^H-MRS, which will be jointly conducted by two hospitals in Chengdu. A total of 129 patients with ME/CFS occurring after COVID-19 and 30 HCs who have fully recovered from COVID-19 will be recruited. After baseline assessment, eligible patients will be randomly assigned to a verum acupuncture (VA), sham acupuncture (SA), or waitlist control group in a 1:1:1 ratio and will receive an 8-week intervention or wait. Figure 1 shows the flow chart of this trial. This study will be conducted in accordance with the Declaration of Helsinki, the Consolidated Standards of Reporting Trials (CONSORT) guidelines (50), and the Revised Standards for Reporting Interventions in Clinical Trials of Acupuncture (STRICTA) guidelines (51). This protocol has been reviewed and approved by the Ethics Committees of the Affiliated Hospital of Chengdu University of Traditional Chinese Medicine and the Public Health Clinical Center of Chengdu and has been registered at ClinicalTrials.gov (NCT07357688).

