##### Waitlist control group

Participants assigned to the waitlist control group will be instructed not to receive any therapy during the 8-week waiting period, but regular health follow-up through telephone will be conducted once a week by an appointed investigator. Furthermore, participants will be able to report their feelings to the investigator at any time. For those whose symptoms worsen during the waiting period, specialists at the Affiliated Hospital of Chengdu University of Traditional Chinese Medicine will be contacted immediately for symptomatic treatment, and intensive symptom monitoring will be implemented until symptoms return to their previous level. For participants whose exacerbated symptoms show no significant improvement or who develop new illnesses, withdrawal from the study will be recommended, and they will be advised to seek appropriate treatment. Participants who complete the 8-week waiting period will receive the same acupuncture treatment as the VA group for free.

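### The adverse-event recording window is tied to the intervention, which the waitlist arm does not have in weeks 0–8, yet event rates are to be compared between the groups

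*Protocol article*

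**What the plan says.** In the section Adverse events and safety, the recording rule reads as follows: "Any adverse events (AEs) or serious adverse events (SAEs) occurring during the intervention, whether related to the intervention or not, will be recorded". The entries go on case report forms. No separate period is given for the waitlist arm.

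The Study design section treats intervention and waiting as alternatives: patients "will receive an 8-week intervention or wait". The Waitlist control group section adds that these patients "will be instructed not to receive any therapy during the 8-week waiting period", and that treatment comes later: "Participants who complete the 8-week waiting period will receive the same acupuncture treatment as the VA group for free".

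That section also describes contact during the wait. There is a weekly call: "regular health follow-up through telephone will be conducted once a week by an appointed investigator". There is open reporting: "participants will be able to report their feelings to the investigator at any time". Specialist contact with closer monitoring is provided "For those whose symptoms worsen during the waiting period".

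The Statistical analysis section says that a chi-square test "will be used to compare the rate of AEs and SAEs between the groups". It does not name the groups or the period.

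**The concern.** Because the rule covers events whether or not they are related to treatment, it is meant to capture background illness as well as needling events. In the article's own vocabulary, however, the waitlist arm has no intervention during the randomised 8 weeks. Under the literal rule, an intercurrent illness in week 4 goes on the CRF for a VA or SA patient and not for a waitlist patient. A needling event in the waitlist patient's later course meets the rule, although it arises after the randomised comparison has ended.

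The waitlist arm is the only untreated randomised source of the background event rate over these 8 weeks. If its events are under-recorded, acupuncture (verum or sham) looks more harmful than it is, and the test responds partly to how data were collected.

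**Working it through.** **1. The passages side by side, for each randomised arm.**

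| | VA and SA | Waitlist |
|---|---|---|
| Weeks 0–8 | intervention | wait, no therapy |
| Inside the recording window as worded? | yes | no |
| After week 8 | no trial treatment described | VA-type acupuncture |
| Inside the window as worded? | no | yes |
| In the planned rate comparison? | yes | most naturally yes |

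The last row is an inference. The statistical paragraphs refer to three groups when they describe baseline comparability and functional connectivity, and nothing limits the safety test to VA and SA.

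**2. Is there a stated figure to reproduce?** No. The article gives no expected event rate and no power for safety. What follows is illustration under assumed values.

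**3. The literal extreme: no waitlist events recorded.** Inputs: 43 per arm (Sample size calculation), and an assumed equal number k of patients with an event in VA and in SA. For counts k, k, 0 the expected count is 2k/3 per arm, and Pearson's statistic reduces to

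X² = k + (2k²/3) / (43 − 2k/3), with 2 degrees of freedom, so p = exp(−X²/2).

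- k = 6 (14%): X² = 6 + 24/39 = 6.62, p = 0.037
- k = 9 (21%): X² = 9 + 54/37 = 10.46, p = 0.005
- k = 13 (30%): X² = 13 + 112.67/34.33 = 16.28, p = 0.0003

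Each result is significant at the planned two-sided 0.05 level, with no true difference assumed.

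**4. Partial capture.** Simulation of the three-arm chi-square test: 43 per arm, the same true risk in every arm, the waitlist arm recording a fraction c of its events, and 20,000 trials per setting (Monte Carlo standard error at most √(0.25/20,000) ≈ 0.4 percentage points). Proportion of trials rejecting at 0.05:

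| Assumed true risk | c = 1 | c = 0.75 | c = 0.5 | c = 0.25 | c = 0 |
|---|---|---|---|---|---|
| 10% | 5% | 6% | 11% | 22% | 47% |
| 20% | 5% | 8% | 23% | 55% | 99% |
| 30% | 5% | 11% | 37% | 80% | 100% |

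The test keeps its level at full capture, is mildly off at three quarters, and is badly distorted when capture is half or less and events are not rare. The article supplies neither the risk nor c, so it does not say which cell applies.

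**5. VA against SA.** Both arms have the same sessions, the same 8 weeks and the same rule, so the gap does not touch this comparison.

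**The case against.** A reader might infer that waitlist events will certainly go unrecorded and that the whole safety comparison is therefore invalid by design. The documents do not support that. The rule does not say that recording is confined to the intervention and forbidden elsewhere. The waitlist arm has weekly health calls, open reporting and monitoring of worsening, so a site would probably learn of a week-4 illness. The Randomization and blinding section speaks of serious events during the trial, without tying them to treatment. A site could reasonably take the intervention to mean the whole 8-week period in every arm.

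A reader might also contrast 24 treatment sessions with about 8 weekly calls and take that ratio as the capture rate. This does not follow either. Under Physical activity monitoring, all participants wear the accelerometer for the 8 weeks and investigators make daily video calls, about 8 × 7 = 56 contacts in each randomised arm. Those calls are for device adherence and are not said to ask about adverse events, but they rule out a simple 24-to-8 comparison.

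Finally, every outcome ends at week 8, and no sentence places the later free course in the comparison. The article is also a condensed account, and detailed event-collection procedures may sit in the full protocol.

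All of this limits the size of the problem without removing it. Learning of an event is not the same as entering it on the CRF, and the article nowhere says that waitlist events are entered. Nor is this a silence left to another document: the article states a window, and that window does not fit one of the three arms being compared.

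**Conclusion.** The point holds as a mismatch between a stated recording window and a planned comparison. As worded, the window omits the waitlist arm's weeks 0–8 and admits its later acupuncture course. Any comparison with the waitlist arm is biased to the extent that its events are under-recorded. VA versus SA is unaffected.

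The size cannot be derived from the article. The figures above rest on assumed, equal background risks, assumed capture fractions and exactly 43 patients per arm. They show that the effect could range from negligible to overwhelming. They do not show that the safety analysis will fail. The change is worth making because the wording governs what reaches the CRF and the correction is nearly free.

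**What to change.** - In Adverse events and safety, replace the reference to the intervention with: *from randomisation until completion of the week-8 assessment, in all three randomised arms*.
- State that events found at the waitlist telephone calls, or reported spontaneously during the wait, are entered in the CRF as AEs or SAEs. Preferably, ask the same adverse-event question in every arm through the daily video calls that are already planned.
- In Statistical analysis, name the groups compared and refer to that window.
- Report events in the waitlist arm's acupuncture course after week 8 separately, outside the randomised comparison.

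The cost is a few sentences, one question added to an existing call, and slightly more adverse-event forms. VA and SA patients will still have more in-person contact than waitlist patients, and the report should say so wherever rates are set against the waitlist arm.
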